## 5.2 Identifying patients

Eligible patients will be identified in the respective multi-disciplinary meetings and out-patient clinics (women’s clinics, urology and radio-oncology departments) at participating sites. A screening and recruitment log will be kept at each site recording all patients who were considered for the study. This will be a secure log holding patient names and details of those who consented to take part. For patients who did not fulfill the eligibility criteria or declined to take part, only a minimal dataset will be recorded, i.e. hospital number, gender and tumour site.

As REQUITE does not interfere with any standard or experimental, diagnostic or therapeutic procedures, patients may be included in REQUITE while participating in any other study/ trial.

The clinical leads representing the recruiting study centres have previously been involved in clinical trials and/or radiogenomics studies. Therefore, the logistics of patient recruitment already established at the participating clinics will be used for this study. Multiple clinics per recruitment centre will be involved, where necessary, to ensure adequate participant enrollment to reach the target sample size.

## 5.3 Consenting patients

Patients deemed eligible for entry into REQUITE will be provided with a verbal and written explanation of the study in accordance with local governance and regulatory departments. After adequate time has been given (a minimum of 24 hours), all queries have been addressed and the clinical team is confident that the patient understands the study and the necessity for long-term follow-up, patients will be consented onto the study.

Consent will be taken by a member of the study team who is GCP trained, suitably qualified and experienced and who has been delegated by the Principal Investigator to undertake this activity (and this delegation is clearly documented on the delegation log).

Consent will be specifically sought for the following:

- use of blood sample and/or DNA in molecular-genetic research
- use of blood sample and/or DNA in future genomic studies
- potential commercialisation

#

# 6.0 STUDY METHODOLOGY

## 6.1 Patient Registration

Issue of each patient’s unique study identifier will be done by allocation of the next sequential REQUITE kit (provided by CIGMR). Each kit will contain a number of bar-coded labels displaying the unique study identifier for that patient, as well as a bar-coded BD Vacutainer EDTA blood tube. The labels can be affixed to other blood tubes, consent form or patient notes as appropriate (see below).

Following signing of the consent form, the ‘Consent’ bar-code label from the next sequential REQUITE kit should be affixed to the consent form, and scanned into the appropriate table on the REQUITE centralised database. This will formally register the patient on the REQUITE study and represent their primary entry in the REQUITE database. The enrolment form confirming patient eligibility for the study should also be completed at this time.

##

## 6.2 Sample Collection and Tracking

Patients who are deemed eligible for the study following consent and all screening evaluations will be asked to gift pre-treatment blood samples that comprise ‘Sample A’ (10ml) and at least one of ‘Sample B’ (2.5ml) or ‘Sample C’ (10ml). A limited number of patients may be asked to give an additional blood sample to enable repeat analyses of the live cell assays for quality control purposes.

CIGMR will print and distribute all the bar-codes to be used in this study in individual REQUITE kits. Each bar-code label will display the following machine readable and human readable information:

- Human readable unique study identifier
- 1D barcode representing the unique study identifier
- Recruiting centre
- Sample type (EDTA blood, PAXgene or Lithium Heparin)

CIGMR will send out batches of individual REQUITE kits to each study centre. Each kit contains a bar-coded EDTA BD Vacutainer blood tube representing ‘Sample A’ in the REQUITE study. Depending on the recruiting site (see below) CIGMR will also provide additional bar-coded labels to be used on a PAXgene tube (Sample B) or a Lithium Heparin tube (Sample C). These labels should be affixed at site to the appropriate tube and blood collected at the appropriate time point (see below).

**Sample A**

- All patients in REQUITE (n ~5,300):

One 10ml EDTA blood sample will be collected either:

1) Prior to the start of radiotherapy for lung cancer patients;

2) Prior to the start of radiotherapy for prostate cancer patients;

3) Prior to the start of chemotherapy or radiotherapy for breast cancer patients*.

* The timing for collection of the blood sample from breast cancer patients is dependent upon the recruiting site (see below).

All EDTA bloods will be stored locally at -80°C as whole blood, no further processing is required. Following blood collection, study centres will scan the bar-code to complete a sample tracking form on the REQUITE centralised database, which can be accessed by CIGMR. This will provide accurate and consistent tracking of samples at study centres and will be used to update the CIGMR Laboratory Information Management System (LIMS).

CIGMR will liaise with each of the study centres regarding the return of frozen EDTA blood samples by courier at regular intervals e.g. every six months or as required. CIGMR will log and receipt the frozen blood samples immediately raising any discrepancies with the originating centre. At an appropriate time point they will process the blood samples to extract DNA; perform both a quality assessment and DNA quantification using Nanodrop technology and dilute to a standard concentration of at least one aliquot and store the undiluted and diluted DNA at two different geographical sites to guard against catastrophic loss prior to transfer to Source Bioscience for genotyping (see Section 6.6.1)

CIGMR will ensure continuous maintenance and management of their storage facility to ensure all equipment is fit for purpose and safe to use. As a certified biobank, they will ensure all laboratory, data and management processes are fully compliant with ISO9001:2008.

**Sample B**

- Patients recruited at CNFT, FPGMX, UGENT, ULEIC, MSSM, INT, KULEUVEN, MAASTRO or third parties associated with these centres (n ~3,500).

One 10ml PAXgene tube will be labelled with the corresponding PAXgene bar-code clearly displaying the same study identifier as used previously for the EDTA sample (Sample A). This PAXgene tube is pre-loaded with 7.5ml of RNA stabiliser and 2.5ml of blood will be drawn from the patient. Bloods will be collected at the same time as ‘Sample A’ either:

1) Prior to the start of radiotherapy for breast cancer or lung cancer patients;

2) Prior to the start of radiotherapy for prostate cancer patients.

This PAXgene blood sample will be stored locally at -80°C as whole blood for future RNA collection and extraction. Note, the samples for RNA analysis will not be used further in REQUITE, but will be a resource for future exploitation in biomarker discovery projects or similar.

**Sample C**

- Patients recruited at UMM, ULEIC, ICM or third parties associated with these centres (n ~1,800)

One 10ml Lithium Heparin (LiH) blood tube will be labelled with the corresponding LiH bar-code clearly displaying the same study identifier as used previously for the EDTA sample (Sample A). The LiH blood sample should be collected at the same time as ‘Sample A’ either:

1) Prior to the start of chemotherapy and radiotherapy for lung patients;

2) Prior to the start of radiotherapy for prostate cancer patients;

3) Prior to the start of chemotherapy and radiotherapy for breast cancer patients.

This sample will be retained in the recruitment centre for immediate analysis in the live cell apoptosis assay work. Each centre will make local arrangements for the transport of samples from the clinical facilities to the analysis laboratory, and temporary storage at 4°C (see Section 6.6.2). For comparative research and quality assurance, this sample may also be used for analysis using other DNA damage and repair assays (see Section 6.6.3).

**Repeat Sample C**

- Patients recruited at ULEIC or third parties associated with this centre (n = 200 maximum)

An additional 10ml Lithium Heparin (LiH) blood tube will be labelled with a duplicate LiH bar-code displaying the same study identifier as used previously. This LiH blood sample will be collected:

1) Prior to the start of radiotherapy from breast cancer patients who previously received chemotherapy.

Or

1. Following completion of radiotherapy at follow up visits

This sample will be retained in the recruitment city for immediate analysis in the live cell assays work. It will represent a repeat of ‘Sample C’ collected at an earlier time point and will be used for the live cell assay work to allow researchers to compare differences between samples collected pre-chemotherapy and post-chemotherapy or pre- and post- radiotherapy. Local arrangements will be made for the transport of samples from the clinical facility to the analysis laboratory, and temporary storage at 4°C (see Section 6.6.2).

**Unused material**

Unused material derived from samples A-C will be processed according to a common protocol followed by all participating sites. Subject to approval from the REQUITE management team this unused material specifically DNA, RNA, lymphocytes and plasma will be stored and made available for collaborators to use in externally funded and ethically approved projects (e.g. gene expression or epigenetic marker studies).

## 6.3 Data Collection

The primary method of data capture in REQUITE is the centralised online database. An online web browser will be available for patients to complete their questionnaires whilst in clinic, or alternatively at home if required. Where patients choose to use a paper based questionnaire then manual data entry must be performed by study centre personnel. Healthcare professionals will also have password protected access for completion of CRFs and file uploads (breast photos and physics data) as detailed below.

**Case Record Forms (CRFs)**

- Enrolment form (eligibility criteria)
- Blood collection form
- Patient factors form (epidemiology)
- Clinical and treatment data collection form
- Health professional toxicity data form (tumour specific; based on CTCAE v4.0)
- Patient reported outcomes questionnaire (tumour specific; based on CTCAE v4.0)
- EORTC Core 30 Quality of Life questionnaire (C30)
- Tumour specific questionnaires including but not limited to BR23
- Withdrawal form
- Outcome data form

**Time points for CRF collection**

CRFs should be completed at routine clinic appointments, or in conjunction with a telephone call e.g. if a patient is attending follow-up near home. Time points specifically include:

- Baseline (prior to start of radiotherapy or within first five days of radiotherapy) Lung cancer patients receiving SBRT should complete CRFs prior to, or on the first day of radiotherapy
- End of radiotherapy (1-2 days prior to or the last day of treatment) for breast and prostate patients. For brachytherapy patients: at the first routine follow-up visit following implantation.
- 3 months from start of radiotherapy (+/- 4 weeks) for lung cancer patients
- 3 months from start of radiotherapy (+/- 4 weeks) for breast cancer patients (ULEIC only)
- 6 months from start of radiotherapy (+/- 4 weeks) for lung cancer patients
- 12 months from start of radiotherapy (+/- 4 weeks)
- 24 months from start of radiotherapy (+/- 4 weeks)
- 36 months from start of radiotherapy (+/- 4 weeks)
- 48 months from start of radiotherapy (+/- 4 weeks)
- 60 months from start of radiotherapy (+/- 4 weeks)

See schedule of assessments for timings of completion of each CRF for each tumour site (Section 12.0).

**Physics File Uploads**

Uploading of physics data and CT images to the REQUITE database can be completed at any point in the follow-up pathway prior to the observational study end. All personal data should be removed before files are uploaded. Only the unique study identifier should be used.

- DICOM-RT files
- CT images and contouring
- DVH data

**Digital Photographs (breast cancer patients only)**

Photographs should be of sufficient quality to show any skin changes (including telangiectasia), breast shrinkage or retraction. Photographs should include both breasts to compare any change between the irradiated and unirradiated breast. Photographs must exclude the head.

Two anterior views of the chest are required, one with hands on the hips and the other with hands raised as far as possible above the head. One lateral view of the chest with hands above the head is also required.

Study centres are advised to follow the guidelines detailed in the REQUITE ‘Photographic Assessment Form’ (Form B4)’ for guidance on taking breast photographs for inclusion in this study. This will minimise inter-centre and intra-centre variation in photographic conditions.

**Time points for digital photographs (breast only)**

- Baseline (prior to start of radiotherapy or within first five days of radiotherapy)
- 24 months from start of radiotherapy (+/- 4 weeks)
- 36 months from the start of radiotherapy (+/- 4 weeks)
- 60 months from the start of radiotherapy (+/- 4 weeks)

## 6.4 Data Handling

All data entered into the REQUITE database by patients and healthcare professionals will be subject to an automatic comprehensive validation check program to identify missing, illogical and/ or inconsistent data before submission can be completed. In addition, the REQUITE data manager will assess data regularly and review any questionable data and correct any data entry errors with the help of the appropriate healthcare professionals.

The exact procedures for data entry and data clarification, including contact details for any related queries will be described in the study specific SOPs and instructions that will be sent to all REQUITE study centres as soon as they have completed the site initiation process. Reminders for any overdue data will also be sent out as necessary.

## 6.5 Radiotherapy

REQUITE is not a trial of radiotherapy, therefore the radiation dose and regimen is not prescribed. However, for breast patients receiving neo-adjuvant chemotherapy, it is important that radiotherapy should not commence until at least one month has elapsed following the end of chemotherapy.

All radiotherapy regimens will follow local standard of care decided by the treating clinician. Treatment details will be documented on the appropriate REQUITE CRF.

For lung cancer patients where possible, the heart should be outlined along with the pericardial sac. The pericardial sac surrounds the heart and extends superiorly to encompass the main pulmonary artery, the ascending aorta and the superior vena cava. Outlining should extend superiorly to the inferior limit of the aortic arch (the aortopulmonary window) and the superior limit of the trunk of the pulmonary artery if it can be identified on the radiotherapy planning CT scan.

For breast cancer patients, where possible, the following guidelines should be followed for heart delineation. Superiorly the heart starts just inferior to the left pulmonary artery. It includes the atria, ventricles, auricles, vessels and fat tissue within the pericardium. Since the cardiac vessels run in the fatty tissue within the pericardium, they should be included in the contours, even if there is no heart muscle visible in that area. Inferiorly, the heart blends with the diaphragm^^[[32]](#footnote-32)^^. For breast delineation, a wire should be used on the CT scan around the palpable breast tissue to define the peripheral edges of the breast. The deep edge is the superficial side of the pectoral muscle/thoracic wall. The superficial edge is the skin. Any visible glandular breast tissue outside these margins should also be included.

For prostate cancer patients, details of the rectum and bladder delineation should be specified on form P3, stating whether the entire rectum is delineated from anus to sigmoid; or alternatively, 2 cm cranial and caudal of the PTV; either as solid or hollow organ. For bladder delineation, it should be specified whether the entire bladder is delineated or the posterior wall only. Additionally, the filling level of the bladder should be stated.

## 6.6 Biomarker Assays

### 6.6.1 Genotyping

Genotyping will be carried out by commercial partner Source Bioscience in their facilities in Eire, UK or Germany.

The selection of genetic markers to be typed will be made by University of Cambridge in association with the University of Leicester and other members of REQUITE. The published literature will be evaluated for high quality genetic studies showing strong evidence of association with one of the clinical radiation toxicity endpoints. These markers will be collated into a single list such that patients for each cancer are typed for all markers. This maximises the chance of validating the associations whether they affect a single or multiple clinical endpoints.

Genotyping will be performed with the best available technology at the time, currently Fluidigm or GoldenGate custom arrays. CNVs would be typed either with a SNP genotyping platform or a qPCR based approach. A genome-wide approach may also be feasible, either by arrays or sequencing. If whole genome data are collected the information from the chosen markers will be extracted for the predictive markers, with the whole data being included in a separate association analysis. Control samples will be repeat typed in each laboratory to ensure reproducibility between sites.

**Genotyping Quality Assurance**

Quality assurance measures are already in place to produce negative controls on each experimental plate, and 5% of the samples from each plate will be duplicated on another plate as a reproducibility check. The genotype assay will be optimised on a panel of 80 unique DNA samples plus 12 duplicates and 4 negative controls. Duplicated samples must give greater than 99% concordance before the assay is accepted. These procedures are currently part of laboratory procedure.

### 6.6.2 Live cell apoptosis assays

The samples will be analysed at three centres: University of Leicester, UK; University of Heidelberg, Germany and University of Montpellier, France. Each centre will follow the current REQUITE standard protocol for ‘Radiation Induced Apoptosis Assays’ to reduce variability between centres. As a quality assurance measure for reproducibility both inter-lab and intra-lab variation will be assessed. Completion of the apoptosis assays will occur in Year 3 when patient `recruitment closes.

### 6.6.3 DNA damage and repair assays

These will be performed at the University of Leicester with lymphocytes from the sample used for the live cell apoptosis assay. Internal standard protocols for the relevant assays will be followed, including but not limited to the Comet and gamma-H2Ax assays.

# 7.0 STATISTICAL PLANS AND DATA ANALYSIS

## 7.1 Power calculations

**Live Cell Assays**

For the apoptosis assays with 800 breast, 600 prostate and 400 lung patient samples there is 80% power to detect relative risks (RR) of >1.31, 1.36 and 1.44 respectively, (α = 0.05, low apoptosis freq = 0.39, toxicity rate = 20%), or a 95% power to detect RR of >1.40, 1.47 and 1.57.

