There is interest in using rapid cell based functional assays for measuring radiosensitivity. Of particular relevance is a flow cytometry method for assessing radiation-induced apoptosis. High toxicity following radiotherapy has been linked with low levels of radiation-induced apoptosis in several independent studies. A number of assays were studied in the past and the apoptosis assay stands out because the findings have been replicated in several independent laboratories^[[8]](#footnote-8),^^[[9]](#footnote-9),^^[[10]](#footnote-10),^^[[11]](#footnote-11),^^[[12]](#footnote-12),^^[[13]](#footnote-13),^^[[14]](#footnote-14)^. The apoptosis assay provides an assessment of the radiosensitivity of a patient at the time of radiotherapy, i.e. incorporating both genetic and epigenetic effects. This work will establish whether the apoptosis assay can be validated within a prospective multi-centre study using a standardised protocol. To do this, the assay will be standardised and quality assurance and control methods set up for cross laboratory analyses. The latter are required for clinical testing. If the assay can be neither standardised nor validated, then definitive evidence will be obtained that further studies using the assay are not warranted.

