**Genotyping**

It is estimated that 2-year toxicity data (1-year for lung) will be available for 75% of enrolled patients. Based on effect sizes observed for genetic associations with radiation toxicity, a power calculation for the genetic assays shows that 1,575 patients for breast and prostate cancer each has 80% power to detect a RR of >1.56 for at least grade 2 toxicity (α = 5 x 10^-5^ for 1000 SNPs, allele freq = 0.25, toxicity rate = 20%), or with more stringent criteria a 90% power to detect a RR >1.66 (α = 1 x 10^-5^, allele freq = 0.25, toxicity rate = 20%). For 825 patients with lung cancer the detectable RR would be 1.78 and 1.92.

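### Section 7.1 overstates what the apoptosis assays can detect: its relative risks are ratios of marker frequency, and the expected 25% loss of toxicity data is left out

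*Protocol*

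**What the plan says.** Section 7.1, Live Cell Assays, gives the sample sizes ("For the apoptosis assays with 800 breast, 600 prostate and 400 lung patient samples") and two sets of detectable effects: "there is 80% power to detect relative risks (RR) of >1.31, 1.36 and 1.44 respectively", "or a 95% power to detect RR of >1.40, 1.47 and 1.57". Its listed inputs are "α = 0.05, low apoptosis freq = 0.39, toxicity rate = 20" per cent. It does not say which group is the numerator of the ratio, whether 0.39 applies to all patients or only to those without toxicity, or whether the test is one- or two-sided.

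The three sample sizes add to 1,800. That is the number of lithium heparin samples to be collected under Section 6.2, Sample C: "Patients recruited at UMM, ULEIC, ICM or third parties associated with these centres (n ~1,800").

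Section 7.1, Genotyping, states: "It is estimated that 2-year toxicity data (1-year for lung) will be available for 75% of enrolled patients". It applies this to its own sample sizes (1,575 is 75% of 2,100; 825 is 75% of 1,100) and describes its RR as one for toxicity of grade 2 or worse.

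Section 2.3 draws a consequence: "If the assay can be neither standardised nor validated, then definitive evidence will be obtained that further studies using the assay are not warranted".

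**The concern.** REQUITE is a prospective cohort, and the question is whether a pre-treatment marker predicts later toxicity. In that setting RR means the risk of toxicity in low-apoptosis patients divided by the risk in the others, and the Genotyping paragraph encourages that reading. Tested on that definition, the printed values fall far short of 80% power. The apoptosis calculation also makes no allowance for missing toxicity data, although the assay can be evaluated only in patients whose toxicity is known.

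At stake is how a failure to validate the assay will be read. Someone who takes Section 7.1 at face value will believe that a 31–44% excess risk of toxicity would be found four times in five. Section 2.3 makes non-validation one of two conditions for saying that work on the assay should stop.

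**Working it through.** **Inputs.** From Section 7.1, Live Cell Assays: N = 800, 600, 400; α = 0.05; low-apoptosis frequency 0.39; toxicity rate 0.20; ratios 1.31, 1.36, 1.44 (80%) and 1.40, 1.47, 1.57 (95%). From Section 7.1, Genotyping: 75% availability of toxicity data. Two-sided testing is my assumption, and it is the choice that reproduces the printed figures.

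**Formula.** For a two-proportion test with pooled variance under the null and no continuity correction, power = Φ[(|p1 − p0| − 1.96·s0)/s1]. Here s0 = √[p̄(1 − p̄)(1/n1 + 1/n0)] and s1 = √[p1(1 − p1)/n1 + p0(1 − p0)/n0].

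**Step 1: reproduce the protocol.** Compare low-apoptosis frequency between patients with toxicity (0.2N) and without (0.8N), with p0 = 0.39 and p1 = 0.39 × ratio. Breast: n = 160 and 640, p1 = 0.39 × 1.31 = 0.511, p̄ = 0.414, s0 = 0.0435, s1 = 0.0440. Then (0.121 − 1.96 × 0.0435)/0.0440 = 0.81, so power is 79.1%.

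| | Breast 800 | Prostate 600 | Lung 400 |
|---|---|---|---|
| Power at the 80% ratios | 79.1% | 79.5% | 79.3% |
| Power at the 95% ratios | 94.6% | 95.3% | 95.1% |
| Ratio solved for 80% | 1.314 | 1.362 | 1.444 |
| Ratio solved for 95% | 1.404 | 1.466 | 1.568 |

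The solved ratios round to all six printed values. The same layout, with allele frequency 0.25 as the marker frequency, gives 80.2% and 90.5% for the genotyping N of 1,575, and 79.6% and 90.1% for 825, against the stated 80% and 90%. Of the layouts tried that keep the stated N, no other reproduced all six apoptosis figures.

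**Step 2: convert to a toxicity relative risk (Bayes' rule).** Breast, ratio 1.31:
- Overall low-apoptosis frequency = 0.2 × 0.511 + 0.8 × 0.39 = 0.414.
- Risk if low = 0.2 × 0.511/0.414 = 0.247.
- Risk otherwise = 0.2 × 0.489/0.586 = 0.167.
- Relative risk = 0.247/0.167 = 1.48.

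Across the three cancers, the 80% ratios convert to 1.48, 1.57 and 1.74, and the 95% ratios to 1.65, 1.81 and 2.06.

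**Step 3: take the printed values as toxicity relative risks.** Now n is split 39:61 by apoptosis status, with risk 0.20/(0.61 + 0.39·RR) in the others and RR times that in low-apoptosis patients. Breast: 0.178 versus 0.234. Power is 48%, 47% and 45% at 1.31, 1.36 and 1.44, and 66%, 66% and 62% at 1.40, 1.47 and 1.57. If 20% is instead the rate in the other group, power at the first set is 54%, 53% and 53%. Solving for 80% power gives relative risks of 1.49, 1.58 and 1.75, close to Step 2.

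**Step 4: apply 75% availability.** Evaluable N = 0.75 × 800, 600, 400 = 600, 450, 300.

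| | Breast 600 | Prostate 450 | Lung 300 |
|---|---|---|---|
| Power at the 80% ratios, protocol's method | 67.0% | 67.4% | 67.2% |
| Power at the 95% ratios, protocol's method | 87% | 88% | 88% |
| Detectable marker-frequency ratio, 80% / 95% | 1.36 / 1.47 | 1.42 / 1.54 | 1.51 / 1.65 |
| Detectable toxicity relative risk, 80% / 95% | 1.58 / 1.81 | 1.70 / 1.98 | 1.91 / 2.32 |

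**The case against.** The strongest reply is that nothing was miscalculated, and that stands. All six figures follow from the listed inputs at the stated N, and the genotyping figures confirm the layout. A reader who finds 45–48% power might infer an arithmetic error, or that each patient was counted twice. The documents do not support either. Doubling N, with 20% as the reference-group rate, gives 1.30, 1.35, 1.43 and 1.39, 1.46, 1.57, which misses five of the six printed values; doubled genotyping samples would give over 99% power where 80% and 90% are stated. The sensitivity of the design at full N is as calculated. What fails is the label, and a reader cannot see this because Section 7.1 never defines the ratio.

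A second reply is that the 75% appears only under Genotyping. But it is worded for enrolled patients generally and concerns toxicity data, which both analyses need.

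A third is that Section 2.3 does not call a null result definitive. That is correct. Its sentence is conditional on the assay being neither standardised nor validated, and standardisation is a separate strand of work with its own quality checks. The stronger reading, that a non-significant result alone would condemn the assay, is not in the text.

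Finally, details of the analysis may sit in the statistical operating procedure or an analysis plan that is not shown. The power statement, however, is printed in the protocol and is relied on there.

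**Conclusion.** The point holds as a mislabelled effect measure plus an omitted data loss. At full N, the toxicity relative risk detectable with 80% power is about 1.5, 1.6 and 1.75, so the excess risk needed is roughly 48–74% and not 31–44%. Independently of the label, power at the printed ratios falls to about 67% (87–88% for the 95% figures) once a quarter of patients lack toxicity data.

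This rests on a two-sided test, 20% as the overall toxicity rate, and the 75% availability carrying over to the apoptosis patients. If availability in that subset lies anywhere between 75% and 100%, power at the 80% ratios by the protocol's method lies between about 67% and 79%.

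Applying both corrections to the printed values gives 36–38% power. A reader might take that as the loss-adjusted power of the protocol's own calculation; it is not, because it also changes the effect measure. It is the power for a true toxicity relative risk of 1.31, 1.36 or 1.44 with 75% of patients evaluable.

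**What to change.** In Section 7.1, Live Cell Assays, state what the ratio compares, which group 0.39 refers to and that the test is two-sided. Then restate the figures for 600, 450 and 300 evaluable patients in one of two ways:

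- as relative risks of toxicity: about 1.58, 1.70 and 1.91 (80% power) and 1.81, 1.98 and 2.32 (95% power); or
- if the ratio of marker frequencies is kept, named as such: about 1.36, 1.42 and 1.51 (80%) and 1.47, 1.54 and 1.65 (95%).

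Relabel the genotyping RR in Section 7.1 in the same way, and wherever it is repeated (Section 1.0 and the REQUITE-AB summary in Section 13.1), since it reproduces by the same layout; its sample sizes already carry the 75%. Have Section 2.3 refer to the restated figures, so that its remark on definitive evidence is read against the effects the data can actually detect.

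The cost is protocol wording and less favourable printed figures. No extra patients or samples are needed.
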